### Outcome Measures

The assessment will focus on behavioral, gait-related as well as neurophysiological markers to gain a deeper understanding of the CMI during dual-task walking. Standardized questionnaires and assessments, as described in the section “Secondary Outcomes,” will be used to collect general health information and used to control for covarying factors.

#### Primary Outcomes

The primary outcome of the present study will be the dual-task cost occurring in over-ground walking with a cognitive secondary task. Gait parameters will be recorded for single and dual task walking, EEG measures will be conducted throughout the entire experiment (ST cognitive; ST walking; DT walking).

##### Cognitive Task Performance

Participants will receive an auditory or visual discrimination task which fits all criteria for the analyses of gait parameters and event-related as well as continuous brain activity. Task performance will be analyzed using response accuracy and response time.

##### Gait Performance

Gait parameters like walking speed, step length, double support time, etc., will be captured by the OptoGait system (Microgate, Italy). The OptoGait utilizes photoelectric bridges between LEDs and photodiodes to record ground contacts. Therefore, two parallel positioned rows of bars frame the area of measurement. The temporal resolution of the OptoGait is 1 kHz, with a spatial resolution of 1.041 cm. The OptoGait has already been cross-validated against a three-dimensional motion capture system (ICC 0.690–0.999; *p* < 0.001; Healy et al., 2019). The heel strike will be used as event to calculate gait parameters such as step length, swing phase, stance phase, double support phase and more. The heel strike has been proven to be the most suitable event for our purposes (Rudisch et al., 2021).

Arm swing and hip rotation will be recorded using the HTC Vive trackers and four lighthouse cameras (HTC Corporation, Taoyuan City, Taiwan). Both measures will be analyzed for regular and natural patterns using the amplitude and variability of the respective measure.

##### Brain Activity Changes

EEG activity will be recorded using 64 active electrodes on an elastic cap (actiCAP snap and LiveAmp 64, Brain Products GmBH, Gilching, Germany) with electrode positions of the 10% system (Oostenveld and Praamstra, 2001) and one electrooculography electrode placed on the cheek for capturing vertical eye movements. Brain activity data will be analyzed on the sensor- as well as source-level. Individual electrode positions will be recorded using a handheld scanner (CapTrak, Brain Products GmBH, Gilching, Germany).

Event-related measures of interest will be event-related potentials (ERPs, e.g., visual P1/N1, P3 over the occipital and parietal cortex, auditory P1/N2, P3 over the temporal and parietal cortex) as well as event-related spectral perturbations (ERSPs, visual and auditory evoked, and event-related desynchronization of mu (10–12 Hz) and beta (18–30 Hz) rhythms during walking). Further analyzed ERPs will be response-related slow cortical potentials (e.g., movement-related cortical potentials like the lateralized-readiness potential at left and right central electrode sites), and eye-movement as well as gait-phase related analysis. EEG data will be analyzed in the time and frequency domain. In addition, functional connectivity measures will be investigated.

#### Secondary Outcomes

Secondary outcome measures will be recorded in order to ensure the eligibility criteria and to control for the influence of various covarying factors.

##### Demographic and General Questionnaire Regarding Participants’ Current State

Demographic data such as age, body height and body mass, sex, and socio-educational status will be collected, as well as data on the current state of health on the respective assessment day. As a possible contributing factor to the impact of the response side (e.g., on reaction time in cognitive tasks), participants will be asked for their handedness in ten everyday life situations.

##### Short Falls-Efficacy-Scale-International

The Short Falls-Efficacy-Scale-International (SFES-I) is a 7-item questionnaire addressing fear of falling during easy and complex physical activities as well as social activities (Yardley et al., 2005). A validated German version is available, the completion time is approximately 10 min.

##### QuickScreen Clinical Falls Assessment Tool—Translated to the German Language

The QuickScreen Clinical Falls Risk Assessment is a multifactorial assessment tool adapted to clinical settings. Measurement properties have already been confirmed in cohorts of community-dwelling older adults. The QuickScreen shows low measurement error, good reliability, and high sensitivity for physical status changes (Tiedemann et al., 2010). The instrument captures information on risk factors of falling in about 10 min. Assessed risk factors are (1) previous falls, (2) medication usage, (3) vision, (4) peripheral sensation, (5) lower limb strength, (6) balance, and (7) coordination. The number of affirmed risk factors is translated into the potential risk of falling for the respective participant, expressed as a percentage. The calculated percentage indicates the risk of falling within the next year. Therefore, a higher value represents a higher risk of falling.

##### Montreal Cognitive Assessment (MoCA)

The Montreal Cognitive Assessment is a one-page 30-items test developed for screening Mild Cognitive Impairment. It involves items to assess a range of cognitive domains, including executive functions, visuospatial abilities, language, attention, working memory, abstraction, and orientation to time and place. The internal consistency of the MoCA is good (Cronbach’s alpha = 0.84; Wong et al., 2018) and a validated German version is available. The duration of the assessment is about 10 min.

##### Short Physical Performance Battery (SPPB)

The Short Physical Performance Battery (Guralnik et al., 1994) assesses the valid physical function of the lower extremity in older people. Participants are required to stand in an upright position under three conditions (Romberg stance, semi-tandem stance, tandem stance). After that, comfortable gait speed is assessed by measuring the time to walk a four-meter track, starting from a standing position and stopping when the first foot is at the four meters line. Finally, a five-time sit-to-stand transfer is completed as fast as possible. Each domain is scored between zero and four points; SPPB overall scores range from zero (low mobility) to twelve (full mobility). Participants with a score less than 8 will be excluded. The SPPB takes about 10 min.

##### Pure Tone Audiometry

Qualified audiologists with their medical-approved equipment will perform the audiometry on-site testing both ears of the participants. When hearing aids are used by the participant during everyday life, the measurement will be performed with and without a hearing aid. Special solutions for this situation will be conducted in cooperation with the hearing aid acoustician.

##### Dual-Task Strategy Assessment

Participants will be asked to answer a customized six yes/no-items questionnaire about the strategy used during dual-task walking with a modified version of the questionnaire used by Wollesen et al. (2017a):

*Did you feel insecure while walking with the addition of the visual task?*

*Did you feel insecure while walking with the addition of the auditory task?*

*I was annoyed by the mistakes I made in the secondary tasks.*

*Did you concentrate more on the secondary tasks compared to gait performance?*

*Did you try to equally allocate attention to walking and the secondary tasks?*

*Was your preferred walking speed slower while walking with a secondary task?*

*(German Translation: Haben Sie sich unsicher gefühlt, als Sie während des Laufens die Farbe der Lichtblitze unterscheiden sollten? Haben sie sich unsicher gefühlt als Sie während des Laufens die Tonhöhe der Töne unterscheiden sollten? Ich habe mich über meine Fehler in den Entscheidungsaufgaben geärgert. Haben Sie sich mehr auf die Entscheidungsaufgabe konzentriert als auf das Gehen? Haben Sie versucht Ihre Aufmerksamkeit gleichermaßen auf Gehen und Entscheidungsaufgabe zu verteilen? Hat die Entscheidungsaufgabe dazu geführt, dass sich Ihre präferierte Ganggeschwindigkeit verlangsamt hat?)*

### Procedure

#### Description of the Testing Procedure

The cross-sectional study will consist of 2 days of measurement for each participant. After recruitment and signing informed consent, participants’ characteristics will be gathered via a standardized assessment (Prescreening) on day one lasting approximately 1.5 h. Questionnaires will be utilized to capture demographic characteristics, health assessment, fear of falls, fall risk, and cognitive capacity. The physical function will be rated by leg strength, gait- and balance testing. Pure tone audiometry and familiarization with the measurement setup of day two will complete the first day of measurement. The utilized instruments are listed in chronicle order of application below:

##### Measurement Day 1: Prescreening to Identify Confounders and Security Risks

a)Demographic and general questionnaire regarding participants’ current stateb)Handedness Questionnairec)Short Falls Efficacy-Scale-International (SFES-I)d)QuickScreen Clinical Falls Assessment Toole)Montreal Cognitive Assessment (MoCA)f)Short Physical Performance Battery (SPPB)g)Pure Tone Audiometryh)Familiarization with the experimental setup

At the end of day one, participants fulfilling the requirements for inclusion in the study will be invited to return on another day for the second set of measurements. The measurements on day two will mainly comprise EEG measurements while sitting and walking under single- and dual-task conditions. The order of measurement conditions will be pseudo-randomized on day two, always starting with a walking condition and then constantly switching between walking and sitting conditions. Dependent on the task instructions, one of the combinations will represent motor-response ipsilateral (cyan-right, magenta-left, high pitch-right, low pitch-left) or contra-lateral (magenta-right, cyan-left, high pitch-left, low pitch-right) to the presentation side (Table 1). Following the questionnaire about the current state of the participant, familiarization trials for auditory and visual stimuli, and 3 min baseline recordings during sitting and walking will take place.

**TABLE 1 T1:** Stimuli number of the cognitive tasks dissociated by task condition, presentation side, cognitive task modality, modality-specific properties, and presentation-response compatibility with shaded entries representing that the correct response is contralateral to presentation side.

[figure not shown]	

##### Measurement Day 2: Dual-Task Walking With EEG

a)General questionnaire regarding participants’ current stateb)Baseline EEG and Gait Performance without response devicec)Single-Task-Walking with a response deviced)Cognitive tasks while sitting (Single-Task-Conditions)e)Cognitive tasks while walking (Dual-Task-Conditions)

Measurement day 2 will take approximately 2.5–3.5 h per participant and will string together conditions of sitting and walking. Breaks will be at least 2 min between the conditions and may be extended as required. At the end of the measurement of day 2, the participants will be asked about their dual-task strategy.

#### Baseline Electroencephalography and Gait Performance Without Response Device

To collect EEG baseline data and to familiarize participants with the setting, participants will first sit quietly for 3 min and then walk at their preferred walking speed within a 10-m gangway of the OptoGait (Microgate, Bolzano, Italy) system without the response device (3 min). Following the baseline measurements, a 2 min break will take place.

#### Single-Task Walking With Response Device

Single-task walking will take place as one of five conditions in pseudo-randomized order. Participants will walk constantly 520 m (400 m within the OptoGait), but with the response devices in their hands. Participants will be able to choose their preferred walking speed and turn around by walking around a cone placed at least 1 m from the ends of the OptoGait gangway. From the single-task walking, we will also extract the distance walked within the first 6 min as a slightly modified measure of the 6-min walk test (ATS Committee on Proficiency Standards for Clinical Pulmonary Function Laboratories, 2002).

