#### Cognitive Tasks While Walking—Dual-Task-Conditions

For the dual-task conditions, a walking time of 6–7.5 min is estimated for each condition, including turnarounds at the end of the gangway. The same visual and auditory stimuli as described in the previous section will be used. Participants will be asked to simultaneously walk up and down the OptoGait gangway. Participants will be able to choose their preferred walking speed and turn around by walking around a cone, placed at least 1 m from the ends of the OptoGait gangway. Five stimuli will be presented each time participants walk the 10 m gangway of the OptoGait. Each task will end after the participants walked 520 m (400 m within the OptoGait) and 200 presented stimuli.

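### The 6-minute distance is read from a walk set at 520 m, so it cannot exceed 520 m and is capped or undefined above a mean course speed of 1.44 m/s

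*Protocol article*

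**What the plan says.** Under Single-Task Walking With Response Device, the Protocol article fixes the length of the walk: "Participants will walk constantly 520 m (400 m within the OptoGait), but with the response devices in their hands". The pace is free: "Participants will be able to choose their preferred walking speed and turn around by walking around a cone". As a variant of the 6-min walk test, taken from this same walk, the section adds: "From the single-task walking, we will also extract the distance walked within the first 6 min as a slightly modified measure". The section gives no minimum duration, no continuation beyond 520 m and no rule for someone who finishes before 6 min.

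Under Cognitive Tasks While Walking—Dual-Task-Conditions, the matching walks have an explicit stopping rule: "Each task will end after the participants walked 520 m (400 m within the OptoGait) and 200 presented stimuli". For these, "a walking time of 6–7.5 min is estimated for each condition, including turnarounds at the end of the gangway".

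On direction, Aims and Research Questions hypothesises that going from single to dual task worsens walking. The Introduction cites lower walking speed under dual-tasking. The Discussion cites it for younger adults in particular, and says that younger and older adults already differ in single-task walking. No section gives a walking speed for any group.

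**The concern.** A 6-min walk distance is meaningful because the time is fixed and the distance is free. Here the distance is fixed as well. A participant who covers 520 m in less than 6 min has not been observed for the full window, so the stated quantity does not exist for that person, or is entered as 520 m whatever the true pace.

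Analysis cannot recover distance that was never walked. If the capped values were reported as ordinary 6-min distances, fast walkers would look slower than they are, the spread would shrink, and any difference between a faster and a slower group would be compressed. A reader told that the test is only slightly modified would not expect a ceiling.

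**Working it through.** **Inputs from the Protocol article.** Course 520 m, of which 400 m lies inside the OptoGait; window 6 min = 360 s; dual-task time 6 to 7.5 min; 200 stimuli per task, 5 per 10 m pass.

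**Inputs assumed, because the article gives none.** Mean and SD of single-task course speed; size of the dual-task cost in speed; turning speed relative to straight-line speed.

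**1. Reproduce the plan's distances.** 200 / 5 = 40 passes; 40 × 10 m = 400 m, as stated. The other 120 m gives 120 / 40 = 3 m per turn, which is compatible with a cone at least 1 m beyond each end.

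**2. Cap.** Recorded distance = min(520 m, 360 s × mean course speed). The cap binds above 520 / 360 = 1.444 m/s.

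**3. The plan's own time estimate.** 520 m in 6 min is 1.444 m/s, and in 7.5 min (450 s) is 520 / 450 = 1.156 m/s. The fast end of the dual-task range therefore lies exactly on the cap.

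**4. Move to the single-task walk.** With dual-task cost c in speed, single-task time = dual-task time × (1 − c). For a participant who needs 6.0 min in the dual task:

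| Assumed cost | Single-task time | Uncapped 6-min distance | Recorded at most |
|---|---|---|---|
| 5% | 5.70 min | 547 m | 520 m |
| 10% | 5.40 min | 578 m | 520 m |
| 15% | 5.10 min | 612 m | 520 m |

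At a 10% cost, everyone with a dual-task time below 6 / 0.9 = 6.67 min is capped.

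**5. Share capped and loss in the mean.** Take course speed as normal with mean m and SD s, and let a = (1.444 − m)/s. The share capped is 1 − Φ(a). The mean recorded speed is mΦ(a) − sφ(a) + 1.444(1 − Φ(a)), and 360 times this is the mean recorded distance. With s = 0.15 to 0.20 m/s:

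| Assumed mean speed | Share capped | True mean distance | Mean recorded distance |
|---|---|---|---|
| 1.2 m/s | 5–11% | 432 m | 428–431 m |
| 1.3 m/s | 17–24% | 468 m | 458–463 m |
| 1.4 m/s | 38–41% | 504 m | 483–490 m |
| 1.5 m/s | 61–64% | 540 m | 500–507 m |

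For two groups at 1.3 and 1.5 m/s, the true difference of 540 − 468 = 72 m would be recorded as 507 − 463 = 44 m (SD 0.15) or 500 − 458 = 42 m (SD 0.20).

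**6. Turns.** The 1.444 m/s is an average over the whole course. If turns are walked at a fraction r of straight-line speed, the straight-line speed at the cap is (400 + 120/r)/360: 1.48 m/s at r = 0.9 and 1.59 m/s at r = 0.7. The means in step 5 must be read as course speeds; read as straight-line speeds, they overstate the share capped.

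**The case against.** The strongest reply is that little depends on this measure. It appears once, as something extracted in addition. It is not among the primary or secondary outcomes, not a term in the ANOVA under Statistical Analysis, and not part of the sample size calculation. Walking speed is already a captured gait parameter, and 400 m of the single-task walk lie inside the OptoGait, so a fast walker's pace is not lost. All of this stands, and it limits the point to one descriptor.

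A second reply is that the rule for early finishers belongs in a fuller document, and that the explicit stopping rule is written for the dual-task walks only. This stands in part. Stopping at 520 m is still the natural reading of the single-task section, and a later scoring rule could only censor or extrapolate; it could not supply the observed 6-min distance that the article says will be extracted.

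A reader might infer more than the article supports:

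- **That mainly the young group is capped.** The article says that single-task walking differs by age but gives no speeds. The ceiling affects whichever group walks faster.
- **That the study's main contrasts are biased.** Those contrasts concern dual-task costs, which do not use the 6-min distance, and no section gives it a role as fitness measure or covariate.
- **That the larger figures in the working are expected values.** They need a mean course speed of 1.5 m/s, which no figure in the article supports.

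**Conclusion.** The point holds as a small internal inconsistency between a fixed distance and a fixed time window. The ceiling of 520 m and the threshold of 1.444 m/s follow from the article's figures alone. That some participants will reach the cap follows from its own dual-task times together with its expectation that single-task walking is faster. How many will do so, and by how much a group difference would shrink, rests on assumed speeds and SDs and should be read as a range. The primary dual-task costs are unaffected. The correction is desirable rather than essential, and it matters only where the 6-min distance is reported or used.

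**What to change.** Replace the 6-min distance with the time to complete 520 m, or with mean speed over the 520 m. Neither has a ceiling. Both should be obtainable from the synchronised recordings described under Data Management, but the article does not list either one, so the investigators should confirm that start and end times of the walk are stored.

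If a 6-min figure is kept, state how early finishers are handled: either treat them as right-censored at 520 m, or report 360 s × mean speed and flag the value as extrapolated, which assumes that the pace would have been held. In either case report the number of early finishers per group.

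The cost is one sentence and no extra testing. The downside is less direct comparability with the standard 6-min walk test, which the plan already modifies.

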#### Cognitive Tasks While Sitting—Single-Task-Conditions

Participants will be asked to perform cognitive tasks (stimulus-discrimination). During these tasks, participants will be wearing the EEG-system, a custom-made spectacle frame with two LEDs attached to present light stimuli in the peripheral visual field. In addition, participants will wear headphones for presenting auditory stimuli. While sitting in the middle of the OptoGait and performing the task, participants will be asked to look in a walking direction. 200 stimuli (in either the visual or the auditory condition) will be presented with a varying inter-stimulus interval (400–800 ms) and a duration of 100 ms. Participants will be asked to react within a time window of 900 ms to the stimuli by pressing a button on the Vive controller in the respective hand. Thus, the maximal trial duration will vary between 1.4–1.8 s. The participant’s response will initiate the next trial and in case no response is given within the required time window, the next trial will start after 900 ms.

Visual task: Visual light stimuli, magenta (red and blue LED) and/or cyan (green and blue LED) flashes, will be presented counterbalanced and pseudo-randomized on the left or right side of the spectacle frame. Participants will have to which color (magenta or cyan) was presented (color discrimination task) with a right/left hand button press.

Auditory task: Auditory stimuli (high and low tone of 1000 and 500 Hz) will be presented for the duration of 100 ms either binaurally or to the left or right side with a volume of 50–60 dB (equals volume of an indoor conversation, Pearsons et al., 1977), regardless of presence and severity of the hearing impairment. Participants will have to indicate which pitch (low or high) was presented (pitch discrimination task) with a right/left hand button press.

#### Cognitive Tasks While Walking—Dual-Task-Conditions

For the dual-task conditions, a walking time of 6–7.5 min is estimated for each condition, including turnarounds at the end of the gangway. The same visual and auditory stimuli as described in the previous section will be used. Participants will be asked to simultaneously walk up and down the OptoGait gangway. Participants will be able to choose their preferred walking speed and turn around by walking around a cone, placed at least 1 m from the ends of the OptoGait gangway. Five stimuli will be presented each time participants walk the 10 m gangway of the OptoGait. Each task will end after the participants walked 520 m (400 m within the OptoGait) and 200 presented stimuli.

### Data Collection, Management, and Analysis

#### Data Collection

Both, single-task (ST) and dual-task (DT) will be investigated in separate conditions in the experiment. For this purpose, over ground walking will serve as the primary task, while secondary tasks comprise visual or auditory stimulus discrimination. The within-subject comparison between conditions will enable the investigation of dual-task costs vs. task-specific demands. Furthermore, a between-subject comparison will allow for comparing the performance of hearing-impaired older persons with healthy young and older adults. All groups will be treated identically to allow for a comparison of results of dual-task performance across groups.

